## Abstract

**Background:**

Studies suggest that *individualized music listening* is an effective, non-pharmacological intervention for improving the quality of life of people with dementia in the institutional care setting. Noting that most people with dementia live at home, we conduct a randomized controlled trial to assess the feasibility and effectiveness of an app-based individualized music listening intervention for people with dementia in the home care setting. The intervention is delivered by family caregivers.

**Methods:**

We will recruit *N* = 130 dyads consisting of one person with dementia living at home and their family caregiver. After a baseline assessment, dyads are randomly assigned by gender to either the intervention or control group. People with dementia in the intervention group listen to individualized music playlists for 20 min every other day for six weeks via the self-developed *Individualized Music and Dementia* app. The control group receives standard care. All dyads complete paper-and-pencil questionnaires six weeks before the start of the intervention (T0), directly before the intervention (T1), directly after the intervention (T2), and six weeks later (T3). During the intervention period, all caregivers also complete daily ecological momentary assessments via the app. During three home visits, a trained project member will observe the dyads and collect hair samples. After the intervention, semi-structured interviews will be conducted to collect information about participants’ experiences with the app and intervention. The primary outcome is the attainment of individual goals established during the baseline assessment. Secondary outcomes are the well-being, physiological stress and quality of life of people with dementia and their caregivers; people with dementia’s behavioural and psychological symptoms of dementia, resistance during care, and reactions to the music; caregivers’ burden of care, positive aspects of care, and caregiving self-efficacy; and the quality of the caregiver-care recipient interaction.

**Discussion:**

Our study will assess the extent to which an app-based individualized music listening intervention is feasible and effective for enhancing the well-being and quality of life of people with dementia living at home and their family caregivers.

**Trial registration:**

German Clinical Trials Register DRKS00025502 and ISRCTN registry ISRCTN68084105, https://doi.org/10.1186/ISRCTN68084105

**Supplementary Information:**

The online version contains supplementary material available at 10.1186/s12888-024-05697-0.

## Background

Around 55 million people worldwide are currently living with dementia, and this number is expected to dramatically increase in the future as populations grow older [1]. People with dementia increasingly need assistance and support as their disease progresses. Most people with dementia live at home, and care is most often provided by a family member or other informal caregiver [2, 3]. There is thus an urgent need for interventions – especially non-pharmacological interventions [4, 5] – that improve the quality of life of people with dementia and their caregivers that can also feasibly be implemented in the home care setting. A particularly important target for intervention is decreasing the behavioural and psychological symptoms of dementia (BPSD) such as agitation, anxiety or depressive symptoms, which significantly reduce the well-being and quality of life of people with dementia [6] and their caregivers [7, 8], as well as negatively impact the quality of interactions between the caregiver and care recipient [9, 10].

*Individualized music listening* (IML) – that is, listening to personally-meaningful music based on one’s own preferences and experiences – has been shown to be an effective non-pharmacological intervention for enhancing the quality of life of people with dementia in the institutional care setting [11]. The use of IML interventions is supported by neuroscientific evidence, which shows that the brain regions associated with long-term musical memory are relatively unaffected by dementia [12]. Thus, people with dementia remember personally-meaningful music very well. Although the precise mechanisms are still unclear, recent reviews of studies conducted in the institutional care setting have concluded that IML interventions have considerable potential for improving the well-being, social behaviour and BPSD (particularly agitation) of people with dementia [13–16]. A very recent randomized controlled trial (RCT) showed that IML reduced agitation, aggression, and disorientation [17], and helped people with dementia accomplish their own, individual goals (e.g., regarding the people with dementia’s social participation and/or mood) [18]. However, reviews have also emphasized that the effects of IML interventions are highly heterogeneous across studies, and more methodologically rigorous studies and large-scale RCTs are urgently needed [13–16].

A further caveat in research on IML is that the vast majority of research on IML interventions has taken place in the institutional care setting (e.g., nursing homes). Thus, the feasibility and effectiveness of IML interventions in the home care setting is uncertain. Differences in, for instance, the characteristics of the care recipients (e.g., dementia severity) or the physical living space of private and institutional settings (e.g., comfort, available distractions) may affect the feasibility and effectiveness of IML interventions. Nevertheless, a handful of quasi-experimental studies provide first evidence that IML delivered in the home care setting effectively reduce distress [19, 20], agitation [21] and pain levels [22] among people with dementia. There is also some evidence that home-based IML interventions benefit caregivers by increasing caregiver self-efficacy [19] or providing caregivers with an opportunity to take a break [20].

Building on existing evidence of the effectiveness of IML in the institutional and, to a much lesser extent, the home care setting, we conduct the first RCT to test the feasibility and effectiveness of a self-developed, app-based IML intervention for people with dementia living at home. The intervention is delivered by family caregivers in the people with dementia’s own home environment. Most existing studies have relied on professional caregivers and/or music therapists to implement the IML intervention. Designing interventions that can be delivered by family caregivers is key to making it possible to implement IML interventions on a wider scale. First evidence suggests that family caregivers can indeed successfully deliver IML interventions in the home care setting [23], although the intervention must be adapted to the caregivers’ technological skills and experience [19, 20].

We expect that our app-based IML intervention can provide a cost-effective, highly acceptable intervention to improve the quality of life and well-being of people with dementia and their caregivers. Previous research has indicated high heterogeneity in how people with dementia react to IML [24]. We therefore focus on *individual* goal attainment as our primary outcome. We additionally examine the effects of the intervention on caregivers and people with dementia’s well-being, BPSD, the caregiving experience, and the quality of caregiver-care recipient interactions.

We also add to the literature by investigating the impact of IML on the physiological stress of caregivers and people with dementia. Although it is plausible that IML benefits people with dementia at least partly by reducing physiological stress, so far few empirical studies have examined how IML impacts indicators of physiological stress (e.g., heart rate, blood pressure). Moreover, most existing studies have focused exclusively on immediate and short-term effects [24]. Existing evidence has been somewhat mixed, with preliminary findings suggesting potential autonomic down-regulation following IML in the short-term (for a review, see Sittler et al., [25]). In our study, we examine the short- and longer-term impact of IML on heart rate variability and, for the first time, cortisol levels in hair. Analysing cortisol in the hair of people with dementia is feasible and also has a number of advantages in pragmatic RCTs [26], and offers a promising methodological approach for investigating the longer-term effects of IML on physiological stress [26].

## Methods

### Design

We conduct an RCT with an intervention and a control group. All participants complete paper-and-pencil questionnaires at four assessment points: baseline (T0; six weeks before the intervention), pre-test (T1; immediately before the intervention), post-test (T2; immediately after the intervention) and follow-up (T3; six weeks after the intervention). During the six-week intervention period, all caregivers additionally complete daily assessments (i.e., ecological momentary assessments) and three home visits take place. During the home visits, a project member conducts behavioural observations and collects hair samples. Provided consent, video recordings will be made. At the last home visit, a project member conducts semi-structured interviews. Figure 1 provides an overview of the design.

**Fig. 1 Fig1:**
[figure not shown]
Overview of the design of the study

### Participants

The RCT is based on dyads consisting of one person with dementia living at home and their family caregiver. To participate in the study, the person with dementia must have medically-diagnosed dementia, be living at home, and have a health care proxy. Exclusion criteria for people with dementia are severe hearing impairment or planning to move to the institutional care setting within the next three months. No restriction is made regarding the age of the participating people with dementia. Exclusion criteria for caregivers are major physical health impairments or progressive illness, psychiatric diagnosis, obvious cognitive impairment, difficulty understanding German, or participation in another study involving caregivers.

### Recruitment

Dyads will be mainly recruited in Thuringia and adjacent regions in Germany. With the assistance of regional cooperation partners (e.g., medical practices; the German Alzheimer Society of Thuringia), we will recruit participants via posters and flyers; online, print and radio media; and project presentations at planned events and support groups for caregivers. Interested caregivers can contact the project team by telephone during office hours, personally at project presentations, via the contact form on the project website at www.musik-demenz.de, or by e-mail. Potential participants will receive detailed information about the study. After checking that the inclusion criteria have been met, the research team will mail potential participants written information about the study and data protection, a consent form and a stamped return envelope. The text will be formulated for caregivers and in simple language for people with dementia. Dyads who have given informed consent form will be included in the study.

### Sample size

Based on prior research on the effects of IML on people with dementia in the institutional care setting [18, 24, 27], we expect that IML will have small to medium effect sizes (f = 0.2) on our outcome variables. Given our two-group design, an α of 0.05, and a power (1 − β) of 0.95, a sample of *N* = 98 dyads will be needed in order to reliably detect effects. Drop out in studies with a similar target group has ranged from 18% [18] to 36% [28]. To account for drop out, we therefore aim to recruit *N* = 130 dyads.

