### Statistical analysis

We will use SPSS (IBM Corp., Armonk, NY) and R (R Development Core Team, Vienna, Austria) to conduct all analyses. We will check whether there are meaningful differences between the baseline characteristics of the IG and CG. In accordance with the CONSORT statement both “intention-to-treat” and “per-protocol” (i.e., using the sample of participants who adequately adhered to the intervention protocol by completing at least five out of the 21 sessions) analyses will be conducted for comparison. We will also conduct sensitivity analyses to investigate whether missing data, baseline differences, or the total number of listening sessions has any impact on the outcomes.

For analysing the effect of the intervention on the primary outcome (i.e., individual goal attainment), caregivers’ GAS-ratings will be averaged for each participant across all specified goals. Then, we will use t-tests to compare the average goal attainment between members of the IG and CG. In the case of baseline differences in the IG and CG, we will conduct regression analyses to assess the impact of the intervention on individual goal attainment while statistically controlling for the relevant variables. In addition, we will calculate and compare the proportion of participants who completely or partially attained their goals, maintained the initial state, or reported mild/ severe deterioration of their goals in each group.

Secondary outcomes (including data from the daily assessments) will be analysed using multilevel models with two levels, with assessment points (level 1) nested in participants (level 2). Average treatment effects will be analysed by including group membership as a level-2 predictor (0 = CG, 1 = IG). Person-level moderator variables will be included only if necessary, in accordance with the results of the sensitivity analyses. For outcomes that will be assessed for people with dementia as well as for their caregivers (e.g., physiological stress), three-level multilevel models will be used to account for within and between dyadic effects. Assessment points (level 1) will be nested in participants (level 2), and participants will be nested within dyads (level 3). Full maximum likelihood estimation will be used to account for any missing data.

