A major strength of the study is that we use a variety of assessment methods and consider the perspectives of people with dementia, their caregivers, as well as external observers and physiological measures of stress. We employ traditional paper-and-pencil questionnaires, app-based questionnaire measures, in-person behavioural observations, video analysis, semi-structured interviews and hair analysis. We consider how IML is related to daily fluctuations as well as longer-term changes. The daily assessments via app help us to avoid retrospective bias and increase the ecological validity of our study. Finally, we consider how IML affects not only scores on standardized measures but also individual goal attainment. Our measures are specifically designed for the target group of people with dementia who have diverse abilities and symptoms, and who may have difficulty communicating. The behavioural observations and measures of acute and chronic stress allow us to assess people with dementia’s well-being without verbal or written communication, and the DeCS coding system [17] was adapted to our non-pharmacological intervention and the observed group of people with dementia. Further strengths of the study include the sufficiently powered sample of dyads and the inclusion of people at all stages and with all types of dementia. However, the study also has limitations: the design does not allow blinding, and the extent to which family caregivers implement the intervention as intended remains to be seen.

The relevance of feasible and effective interventions that improve the quality of life of people with dementia living at home and their caregivers is evident. Our study will demonstrate the extent to which an app-based IML intervention for people with dementia living at home can be delivered by family caregivers and improve the well-being of people with dementia and caregivers, as well as improve the caregiving experience. Insight regarding the acceptance and usability of the app and the tablet will inform further development of the app and other digital assistance technologies. A sustainability concept is being developed for the continuation of IML in practice.

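### The primary two-group t-test has about 50% power at N = 98 and f = 0.2, not the stated 95%, so the trial is not sufficiently powered for its primary outcome

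*Protocol article*

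**What the plan says.** In the protocol article, Methods, Sample size, the authors write: "we expect that IML will have small to medium effect sizes (f = 0.2) on our outcome variables". The calculation continues "Given our two-group design, an α of 0.05, and a power (1 − β) of 0.95", and finds that 98 "dyads will be needed in order to reliably detect effects". Drop-out in similar studies is put at 18% to 36%, and the recruitment target is 130. The section names no statistical test, number of measurements or correlation between measurements.

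Under Primary outcome, the article defines goal attainment after six weeks, rated from -2 to +2 against goals set at T0. Under Statistical analysis, the ratings are averaged over each participant's goals, and "we will use t-tests to compare the average goal attainment between members of the IG and CG". A regression adjustment is planned only if the groups differ at baseline.

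The Discussion then states: "Further strengths of the study include the sufficiently powered sample of dyads".

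**The concern.** The stated inputs and the stated primary test together fix the power, and it does not come to 95%. The primary outcome gives one score per participant, so the comparison gains nothing from repeated measurement. A standardised difference of 0.4 is modest for a two-sample comparison, and 49 dyads per group is too few to detect it with high probability.

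A reader told that the trial has 95% power may take a non-significant primary result as good evidence that the planned effect is absent. If true power is near 50%, the trial would miss that effect about half the time, and a null result would say little about it. This is the only power statement in the article that covers the primary outcome, and the Discussion counts it as a strength.

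**Working it through.** **Inputs from the article**
- f = 0.2, α = 0.05, power 0.95, two groups, N = 98, target 130, drop-out 18% to 36% (Sample size).
- Two-group t-test on the mean rating (Statistical analysis).

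**Assumptions, because the article does not state them**
- f is Cohen's f.
- Allocation is 1:1, which is the most favourable case for power.
- The test is two-sided; the one-sided result is given as a variant.

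**Step 1. Can 98 be reproduced from the stated inputs?**

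For two equal groups, d = 2f = 2 × 0.2 = 0.4.

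Normal approximation: n per group = 2(1.960 + 1.645)² / 0.4² = 2 × 13.0 / 0.16 ≈ 162.4, so 163.

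The exact noncentral t gives 164 per group, N = 328. One-sided it gives 136 per group, N = 272. For 80% power, two-sided, it gives 100 per group, N = 200. So 98 is not reproduced; the two-sided requirement is 328 / 98 ≈ 3.3 times the stated figure.

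**Step 2. Power of the primary t-test**

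The noncentrality parameter is δ = d·√(n₁n₂/(n₁+n₂)), with n₁ + n₂ − 2 degrees of freedom.

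At 49 per group, δ = 0.4 × √24.5 = 1.980. The two-sided critical value on 96 df is 1.985. The noncentrality almost equals the critical value, so power is 0.500. One-sided, the critical value is 1.661 and power is 0.626.

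| Dyads analysed | Basis | Two-sided power at d = 0.4 |
|---|---|---|
| 98 | stated requirement | 50% |
| 130 | no drop-out | 62% |
| 107 | 130 × 0.82 = 106.6 | 54% |
| 83 | 130 × 0.64 = 83.2 | 44% |

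**Step 3. What 98 dyads can detect**

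Solving the same expression for d at 49 per group gives d = 0.57 (f = 0.29) for 80% power and d = 0.74 (f = 0.37) for 95% power, against the assumed 0.40.

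**Step 4. Where 98 might come from**

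For a repeated-measures group-by-time interaction, λ = f²Nm/(1 − ρ). With m = 4 measurements and ρ = 0.1, λ = 0.04 × 98 × 4 / 0.9 = 17.42 on 3 and 288 df. Power is 0.950, and 98 is the smallest even N that reaches 0.95.

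Other unstated inputs also give 98:
- An interaction with 3 measurements, ρ = 0.5 and a nonsphericity correction of 0.6.
- An overall regression F-test with f² (not f) = 0.2 and 4 predictors.

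These are examples, and the article does not show which, if any, was used. None of them is a two-sample t-test on a single score.

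**Step 5. Could covariate adjustment close the gap?**

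Adjusting for a covariate with correlation r to the outcome raises the effective d to 0.4/√(1 − r²). At 49 per group, r = 0.5 gives 62% power and r = 0.7 gives 78%. Reaching 95% needs r of about 0.84. The planned adjustment is conditional on baseline differences, and the article assumes no such correlation.

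**The case against.** The strongest reply is that the Sample size section never says the 98 was calculated for the primary t-test. It speaks of outcome variables in the plural. Most secondary questionnaire outcomes are measured at T0 to T3 and analysed with multilevel models, and a group-by-time calculation with four measurements and a correlation of 0.1 gives exactly 98. A condensed article may also leave the test family and correlation to a fuller protocol. On this reading the problem is a mismatch between the sample-size basis and the primary analysis, and the arithmetic itself may be sound.

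Much of this is fair. The origin of 98 cannot be settled from the article, the missing inputs alone are not the fault, and the sample may be adequate for some longitudinal secondary outcomes. But the plural wording includes the primary outcome, and the article gives no other justification for it. If the figure belongs to a group-by-time interaction, the primary t-test has no power calculation behind it.

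A second reply is that sidedness and allocation are unstated. That changes the size of the shortfall but does not remove it: a one-sided test reaches 63%, and unequal allocation would lower power.

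A third is that nothing in the article says a null result would be taken as evidence against the intervention. That is true. The risk lies in how a 95% power claim invites readers to interpret such a result.

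**Conclusion.** The concern holds. At the planned effect (f = 0.2, d = 0.4), 98 analysed dyads give the primary t-test 50% power two-sided or 63% one-sided, against the stated 95%. Reaching 95% would take 328 or 272 dyads respectively. Over the article's own drop-out range, recruiting 130 leaves two-sided power of about 44% to 54%.

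The result rests on reading f as Cohen's f and on 1:1 allocation. For the primary outcome, neither the statement about reliably detecting effects nor the claim of sufficient power is supported. Whether the sample is adequate for particular secondary outcomes cannot be judged from what the article states.

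**What to change.** Keep the recruitment target of 130 and correct the text.

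- **Sample size:** state that with 98 analysed dyads the two-group comparison of mean goal attainment has about 50% power (two-sided, α = 0.05, 1:1 allocation) at d = 0.4, that is f = 0.2, and 80% power at d of about 0.57. If a one-sided test is intended, say so and give 63%. Remove or qualify the statement about reliably detecting effects.
- **Origin of 98:** if it was calculated for a group-by-time interaction on secondary outcomes, say so, and preferably give the number of measurements and the correlation.
- **Discussion:** remove the sufficient-power claim, or limit it to the outcomes for which a calculation supports it. Add that a non-significant primary result does not exclude an effect of d = 0.4.

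The cost is a rewritten sample-size paragraph, a changed Discussion sentence and a less favourable stated power. No additional participants are needed.

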### Procedure

#### Baseline assessment

All caregivers will receive a paper-and-pencil questionnaire per mail with a stamped return envelope. The questionnaire will assess sociodemographic and other control variables (e.g., sleep quality, physical complaints), as well as the caregiver’s well-being and perceptions of the caregiving experience. Caregivers will also provide information about their perceptions of the well-being and BPSD of the person with dementia, and the quality of the caregiver-care recipient interactions. A research assistant will contact the caregiver by telephone to debrief the completed questionnaire and ask caregivers about depressive symptoms of the person with dementia. Caregivers will also be asked to formulate at least one goal for the person with dementia to accomplish during the six-week intervention period. Caregivers will describe observable criteria by which accomplishment of the goal can be determined.

